#### Confounding Factors

Potential confounding factors were identified a priori based on a literature review and clinician expertise, and include age, sex, BMI, sleep duration, symptoms before starting PAP therapy, occupational status, highest education level, bed partner, comorbidities, smoking status, alcohol consumption, apnea-hypopnea index at the time of diagnosis, and prescriber specialty. Factors consistently described as being associated with PAP therapy adherence or persistence will be automatically included in statistical models comparing the effect of service on adherence or persistence. Other potential confounding factors will be selected based on their association with adherence or persistence in a univariate analysis. Full details of the confounding variables considered and the supporting sources are provided in Multimedia Appendix 2. Quantitative bias analysis will be performed to evaluate the impact of unmeasured confounders using a metric named the e-value [34]. The e-value can be defined as the strength of association that an unmeasured confounding factor would need to have in order to explain away the observed association.

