### Participants

#### Process for Selecting Patients

Eligible participants are adults (aged 18 years and older) who started PAP therapy between January 1, 2019, and December 31, 2023; for whom PAP services were delivered by an ALH affiliate in France, Belgium, Spain, or Portugal; and had a valid email address or smartphone number.

Potential participants were identified by applying these inclusion criteria to the data sourced from each home support provider database. In France and Portugal, all patients who met the above inclusion criteria were informed about the study. In Spain and Belgium, which have regional- or hospital-level regulatory processes, potential participants are only included from representative investigational sites. After providing the information about the study, patients who either consented to participate (Portugal, Spain, and Belgium) or did not “opt-out” (France) are enrolled in the study. These processes are described in more detail in the Ethical Considerations section.

The digital and decentralized nature of the study using e-consent and an electronic patient-reported outcome (ePRO) tool means that patients are not directly recruited by investigators. Instead, a secure electronic solution, [name], is used to provide direct and individual information about the study, obtain consent, and provide access to the web-based questionnaire. This solution is compliant with European and French legislation and regulations on the protection of personal data, as well as ethical guidance about patient’s rights management. Its technology is powered by blockchain thus guaranteeing full traceability on e-consents.

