### Limitations

Selection bias cannot be entirely ruled out because participants were required to have a valid email address or smartphone number to be eligible for the study. This may lead to underrepresentation of certain subgroups of PAP users, such as older adults. Patients who answer the questionnaire might also differ from those who do not answer it. In addition, this study will only include individuals who use PAP supplied by a home support provider affiliated with ALH and it is possible that the level or content of additional services may differ slightly from other home support providers in the same country. To assess the potential impact of such biases, we will compare the characteristics of our study population with published data on OSA, focusing on age, sex, and disease severity.

Data from the ePRO tool may be subject to recall bias and inaccuracy because participants will complete the web-based questionnaire at variable periods of time since the start of PAP therapy (up to 5 years later for those who started PAP in 2019) and medical data will directly be provided by the patient. Confounding bias other than the key confounding factors considered is another limitation, particularly with respect to medical follow-up (data that will not be collected in this study).

Finally, the period over which this study was conducted included times before and during the COVID-19 pandemic (including lockdowns), and the worldwide recall of a PAP device made by Philips Respironics [36]. Sensitivity analyses will be performed to determine whether these factors had any influence on the overall study findings.

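### No calendar term appears in the printed confounder list or main models, although PAP starts span 2019-2023 and the plan itself treats period events as possible influences

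*Protocol article*

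**What the plan says.** Eligible patients are adults who "started PAP therapy between January 1, 2019, and December 31, 2023" (Process for Selecting Patients). Start date is therefore known for everyone included.

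The Confounding Factors section explains where its candidates come from: "Potential confounding factors were identified a priori based on a literature review and clinician expertise". Those it names begin with demographic, sleep, symptom and social factors and other illnesses, and the list closes with "smoking status, alcohol consumption, apnea-hypopnea index at the time of diagnosis, and prescriber specialty". There are two routes into the models. Factors consistently reported to affect adherence or persistence are forced in. For the rest: "Other potential confounding factors will be selected based on their association with adherence or persistence in a univariate analysis". On where the complete list can be found, the section says: "Full details of the confounding variables considered and the supporting sources are provided in Multimedia Appendix 2".

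Table 2 and Multilevel Models specify linear or logistic mixed models with service level as fixed effect, country as random effect and the selected confounders. No calendar term is stated.

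Limitations notes that "the period over which this study was conducted included times before and during the COVID-19 pandemic", and also names the device recall. Sensitivity Analyses plans to remove data from lockdown periods and to analyse before and after June 2021.

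**The concern.** The plan suspects that calendar time affected PAP use, and it records start date for every patient. As printed, however, the main estimate is not adjusted for it. If the listed factors are the whole candidate pool, neither the forced route nor the univariate screen can bring start date in. The e-value does not fill the gap, since it addresses unmeasured confounders and this one is measured.

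The mix of start years could differ between service levels for two reasons:

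- The Introduction says that service content, visits and telemonitoring differ by country, and Study Rationale says that some countries have changed their patient pathway.
- Ethical Considerations describes opt-out in France and opt-in elsewhere, with the invitation coming up to about five years after start. Opt-in consent may depend on how recent the start was.

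A country random intercept absorbs average differences between countries. It does not handle service levels that shift over time within a country. Nor can it separate start-year mix from service where service is set by country.

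The study is very large, so a small systematic difference could be statistically significant, and the stated purpose includes informing tariffs.

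**Working it through.** The plan gives no figure for this point, so there is none to reproduce. The check is a comparison of the text, followed by an illustration on assumed inputs.

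**Text**

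1. Start window (Process for Selecting Patients): 1 January 2019 to 31 December 2023, i.e. 5 years.
2. Listed confounders: age, sex, BMI, sleep duration, symptoms, occupation, education, bed partner, comorbidities, smoking, alcohol, apnea-hypopnea index, prescriber specialty. That is 13 factors with no calendar term.
3. Model terms in Table 2 and Multilevel Models: service level, country, selected confounders. No calendar term.
4. Handling of period events (Sensitivity Analyses, Limitations): removal of lockdown data, and analyses before and after June 2021. The text does not say whether that split is by start date or by date of data collection.

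**Illustration (every input assumed, none from the documents)**

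Assume no true service effect, starts uniform over 5 years, a linear trend in use of g h/day per year, and a high-service share that moves linearly from p0 to p1. The spurious difference is g × cov(service, time) / var(service), where cov = ((p1 − p0)/5) × 25/12 and var = 0.5 × 0.5 = 0.25, since the average share is 50% in each case.

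- Constant share: cov = 0, bias 0.
- 40% to 60%: cov = 0.04 × 2.083 = 0.083, ratio 0.333. For g = 0.05 to 0.10, bias is 0.017 to 0.033 h/day.
- 20% to 80%: cov = 0.12 × 2.083 = 0.25, ratio 1.0. Bias is 0.05 to 0.10 h/day.

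A simulation of one million patients with SD 2 h/day gave 0.016 and 0.026 for the second case and 0.048 and 0.100 for the third. After adjustment for start time the estimates lay between −0.009 and 0.004 in these two cases.

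**What a June 2021 split would do, if made by start date**

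The strata are 29 and 31 months long (2.42 and 2.58 years). The share of start-date variance left within them is (29/60 × 2.42² + 31/60 × 2.58²) / 25 ≈ 0.25, so about 75% is removed. In the 20% to 80% case the simulated difference within strata falls to 0.013-0.033 h/day. The split therefore helps without removing a smooth trend, and it does not change the headline estimate.

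**The case against.** The strongest objection is that the list does not claim to be complete. It is introduced as "and include age, sex, BMI, sleep duration, symptoms before starting PAP therapy, occupational status, highest education level, bed partner, comorbidities", and the full details sit in Multimedia Appendix 2, which is not shown. A reader might infer that start date has been excluded from the main models. The documents do not support that: they show only that it is not printed, so the recommendation has to be conditional on the appendix.

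Second, the two named events are already addressed. This stands in part. The planned analyses show whether results change, but they leave the main estimate unadjusted, and the basis of the June 2021 split is not stated.

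Third, start date confounds only if it is associated with service level, and no start-year mix by country or service level is given. Differences between countries are not differences over time. The pathway changes carry no dates, and no passage links consent to recency of start. Outcomes are measured at fixed times after start, so unequal follow-up does not by itself enter the 1- to 12-month comparisons. All of this stands: the path is plausible but not shown.

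Fourth, a reader might put a firm size on the bias. For example, an assumed 20-40 point imbalance in starts after mid-2021 times an assumed 0.2-0.4 h/day period effect gives 0.04-0.16 h/day (0.20 × 0.2 to 0.40 × 0.4). Neither input is in the documents, and a split at June 2021 by start date would remove nearly all of that imbalance. Calling it many times the standard error is also unsupported. No SD or group split is given, and a patient-level standard error is a poor yardstick with four countries.

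Fifth, forcing a country-by-period interaction into every model could absorb the contrast under study where service is set by country and period. By quarter that is 4 × 20 = 80 cells. This stands, and it rules the interaction out of the main models.

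**Conclusion.** The point holds in a limited form. As printed, neither the confounder list nor the main models contain a calendar term, although starts span five years, start date is known for all, and the plan regards period events as possible influences. Leaving these to date-cut sensitivity analyses is weaker than adjusting the main estimate.

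The size and direction of any bias cannot be derived from the documents. They depend on the start-year mix by service level and on the period effect, neither of which is given. The 0.02-0.10 h/day in the illustration shows only what particular assumed shifts would produce; with an equal mix the bias is zero. The conclusion also assumes that Multimedia Appendix 2 does not already include start date. The change is worth making because it is simple and nearly free, not because a material bias has been demonstrated.

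**What to change.** Check whether Multimedia Appendix 2 includes year or date of PAP start as a forced covariate. If it does, say so in the Confounding Factors section. If not:

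- Add year of PAP start, or a smooth function of date such as a spline, as a forced main effect in every adherence and persistence model. Do not leave it to univariate screening.
- Keep the planned lockdown and June 2021 sensitivity analyses, and state whether the June 2021 split is by start date or by date of data collection.
- Tabulate start year by service level and country, so that readers can see whether the mix differs.
- Use a country-by-period term only as a sensitivity analysis, with a note that it can absorb the service effect where service is set by country and period.

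The cost is 4 degrees of freedom for five start years (5 − 1), or a similar number for a smooth term. No new data are needed, because start date defines eligibility.

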**Methods:**

This real-world, ambispective, cohort study—conducted in France, Belgium, Spain, and Portugal—will recruit adults with OSA who started PAP therapy between 2019 and 2023 and were followed by an Air Liquide Healthcare home support provider. Given the large number of eligible participants (around 150,000), the study will use a decentralized and digital approach. A patient video will present the study objectives and the participation process. A secure electronic solution will be used to manage patient information and consent, as well as to administer a web-based questionnaire. Retrospective data, collected during routine patient follow-up by home support providers, include the level of service and device data, notably PAP use. Prospective data collected using an electronic patient-reported outcome tool include health status, OSA-related factors, patient-reported outcomes including quality of life and symptoms, OSA and PAP literacy, patient-reported experience, and satisfaction with PAP therapy and service. Hierarchical models, adjusted for preidentified confounding factors, will be used to assess the net effect of home support provider services on PAP adherence and persistence while minimizing real-world study biases and considering the influence of country-level contextual factors. We hypothesize that higher levels of home support provider services will be positively associated with adherence and persistence to PAP therapy.

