#### Statistical Analysis

Statistical analyses will be performed according to a predefined statistical analysis plan (Table 2).

**Table 2 table2:** Statistical analysis plan details.

Objectives	Main outcomes	Key explanatory variables	Statistical methods
Compare PAP^a^ adherence and the PAP therapy persistence rate between different levels of home support provider service	PAP adherence: (1) mean number of hours/day of PAP use and (2) adherent patients defined as those with mean PAP use ≥4 hours/day PAP persistence: (1) percentage of days with PAP use, (2) patients still in therapy, and (3) patients still in therapy and adherent	Fixed effect: Level of service (standard of care, personalized care plan, or high service level) Random effect: Country	Multilevel model adjusted for selected confounding factors
Identify service components that influence PAP adherence and persistence	PAP adherence: (1) mean number of hours/day of PAP use and (2) adherent patients defined as those with mean PAP use ≥4 hours/day PAP persistence: (1) percentage of days with PAP use, (2) patients still in therapy, and (3) patients still in therapy and adherent	Fixed effect: Frequency of interactions, content of support, personalization of support, and telemonitoring Random effect: Country	Multilevel model adjusted for selected confounding factors
Identify factors associated with PAP adherence and persistence	PAP adherence: (1) mean number of hours/day of PAP use and (2) adherent patients defined as those with mean PAP use ≥4 hours/day PAP persistence: (1) percentage of days with PAP use, (2) patients still in therapy, and (3) patients still in therapy and adherent	Fixed effect: Frequency of interactions, content of support, personalization of support, telemonitoring, sociodemographic characteristics, OSA^b^-related clinical characteristics, and characteristics of PAP therapy Random effect: Country	Multilevel model
Descriptive Analysis	Sociodemographic characteristics OSA-related clinical characteristics OSA and PAP literacy Experience with PAP therapy Experience with home support provider support Quality of life Home support provider PAP-related service	N/A^c^	Usual descriptive statistics: Analysis by country
Describe patterns of PAP use	Mean PAP use categories over time	N/A	Data visualization such as Sankey diagrams

^a^PAP: positive airway pressure.

^b^OSA: obstructive sleep apnea.

^c^N/A: not applicable.

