#### Sensitivity Analyses

Sensitivity analyses will be performed after removal of data collected during the COVID-19 lockdown periods, and before and after June 2021 (the time of the Philips Respironics world product recall [35,36].

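### Choosing the non-forced confounders by univariate association with the outcome can drop a measured confounder from the service-level comparison; one adjustment set fixed in advance should replace it

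*Protocol article*

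**What the plan says.** The Confounding Factors section of the protocol article works in three steps.

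- Candidates are named beforehand: "Potential confounding factors were identified a priori based on a literature review and clinician expertise". Thirteen are listed, from age to prescriber specialty, with full details left to Multimedia Appendix 2, which is not shown.
- Some are forced in: "Factors consistently described as being associated with PAP therapy adherence or persistence will be automatically included in statistical models". The main text does not say which ones.
- The remainder are screened: "Other potential confounding factors will be selected based on their association with adherence or persistence in a univariate analysis". No cut-off is given, and association with service level plays no part.

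Table 2 (Statistical Analysis) carries the result into the main comparison of service levels, described as "Multilevel model adjusted for selected confounding factors". That comparison has two adherence outcomes ("PAP adherence: (1) mean number of hours/day of PAP use and (2) adherent patients defined as those with mean PAP use ≥4 hours/day") and three persistence outcomes ("PAP persistence: (1) percentage of days with PAP use, (2) patients still in therapy, and (3) patients still in therapy and adherent"). According to the Methods paragraph of the abstract, the models "will be used to assess the net effect of home support provider services on PAP adherence and persistence".

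**The concern.** A net effect of service is a causal quantity. A factor biases it when the factor is related both to service level and to the outcome. The stated screen looks only at the outcome, and only at the crude association. That crude association mixes the factor's own effect with the part that runs through service level. When the two have opposite signs they can nearly cancel, and a genuine, measured confounder then looks irrelevant and is left out.

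The rule also leaves open whether there is one set or several. If it is applied outcome by outcome, hours of use and persistence could be adjusted for different factors, and differences between their service effects would be harder to interpret.

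The planned e-value analysis does not help, because it addresses unmeasured confounders and not measured ones that were screened out. Nor does sample size give a reason to select: about 100,000 patients can support the whole a priori list.

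**Working it through.** The plan gives no figure for the effect of the selection rule, so there is none to reproduce. What follows is an illustration on assumed inputs.

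**From the documents.** About 100,000 included patients (Sample Size: 150,000 × 0.70 = 105,000, in line with the rounded figure); 13 listed factors; 2 + 3 = 5 main outcomes; an ePRO population that is a subset of unstated size (Patient Datasets). In Table 1, eight of the 13 factors come from the ePRO tool alone: occupation, education, bed sharing, sleep duration, smoking, alcohol, comorbidities and symptoms.

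**Assumed.** Two service levels S and a binary factor C, each with 50% prevalence; service adds bS = 0.5 h/day; SD 2.3 h/day; two-sided p<0.05 screen; ePRO population of 30,000, with 10,000 also shown in step 2; independent patients with no country effect.

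**Step 1: bias when C is dropped.** Let bC be the effect of C on hours and d the difference in the share of C between service levels (with 50% margins, also the difference in service level between C groups).

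- Crude association of C with hours = bC + bS × d. It is zero when bC = −bS × d.
- Bias in the service effect if C is omitted = bC × d, which then equals −bS × d². Relative to bS this is d².

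| d | bC (h/day) | Bias (h/day) | Relative bias |
|---|---|---|---|
| 0.2 | −0.10 | −0.02 | 4% |
| 0.3 | −0.15 | −0.045 | 9% |
| 0.4 | −0.20 | −0.08 | 16% |
| 0.6 | −0.30 | −0.18 | 36% |

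**Step 2: what the screen would keep.** At n = 100,000 a correlation of 1.96/√100,000 = 0.0062 reaches p<0.05. The crude difference detected with 80% power is (1.96 + 0.84) × 2.3 × √(1/n1 + 1/n0), where n1 and n0 are the numbers with and without the factor:

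| n | Factor prevalence 50% | Factor prevalence 10% |
|---|---|---|
| 100,000 | 0.041 h/day | 0.068 h/day |
| 30,000 | 0.074 h/day | 0.124 h/day |
| 10,000 | 0.129 h/day | 0.215 h/day |

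Only very weak or nearly cancelled factors are therefore lost at full size, and more are lost in a smaller subset.

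**Step 3: simulation, 200 runs per scenario, true service effect 0.50 h/day.**

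| bC, d | Crude association | n | C dropped | Mean estimate after screen |
|---|---|---|---|---|
| −0.2, 0.4 | 0 | 100,000 | 92% | 0.43 |
| −0.3, 0.6 | 0 | 100,000 | 95% | 0.33 |
| −0.25, 0.4 | −0.05 | 100,000 | 8% | 0.49 |
| −0.25, 0.4 | −0.05 | 30,000 | 56% | 0.45 |
| −0.2, 0.3 | −0.05 | 100,000 | 6.5% | 0.50 |
| −0.2, 0.3 | −0.05 | 30,000 | 52% | 0.47 |
| +0.2, 0.4 | +0.40 | 100,000 | 0% | 0.50 |

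Adjusting for C regardless of the screen returned 0.50 in every scenario.

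**Step 4: can the sets differ between outcomes?** Take bC = −0.2 and d = 0.4 for hours (crude association 0). For persistence take a probability of 0.80 + 0.03 × S − 0.04 × C, so that the crude association is −0.04 + 0.03 × 0.4 = −0.028. At n = 100,000 the same factor was kept for hours in 4.5% of runs and for persistence in 100%. Screening each outcome separately gave different sets in 95.5% of runs. This scenario was built to show that it can happen; it says nothing about how often.

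**The case against.** The strongest reply is that little is lost. Factors with consistent evidence are forced in, so only those with weaker or mixed evidence face the screen, and with about 100,000 patients nearly all of them would pass. That stands, and it limits the size of the point. It also means that the screen achieves almost no simplification, while the failure it can produce is the harmful kind.

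Several stronger conclusions may tempt a reader, and the document does not support them.

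- **Each outcome certainly gets its own set.** The wording refers to adherence or persistence and also permits one common set. The rule can give different sets; it need not.
- **The screen uses p<0.05.** No cut-off is stated, so every retention figure above depends on that assumption.
- **The service effect will be biased by 36%.** That needs a 60-point imbalance and exact cancellation. With bC = −0.3 and d = 0.5 instead of 0.6, the crude association is −0.3 + 0.25 = −0.05 h/day. In the simulated scenarios with that crude association, the factor was missed in only 6.5% to 8% of runs at 100,000.
- **Year of PAP start is missing from the adjustment.** The listed factors are introduced as included ones, with the rest in an appendix that is not shown. The sensitivity analyses also cover lockdown periods "and before and after June 2021". The absence cannot be established.

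Two practical objections shape the remedy. Restricting the set to factors recorded at or before PAP start could remove six of the 13, because Table 1 times occupation, education, bed sharing, sleep duration, smoking and alcohol at ePRO completion. And forcing ePRO factors into every model confines that analysis to responders, who may differ from non-responders according to the Limitations section. The plan already admits ePRO factors to these models, so the second issue is not new, but it has to be handled openly.

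**Conclusion.** The point holds as a weakness in a rule the document states, not as a missing detail. Outcome-only univariate screening does not suit a net-effect aim: it can drop a measured confounder, and it leaves unclear whether the five main outcomes share one adjustment set.

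The expected effect is small in the full population and larger in the ePRO population. In the zero-crude-association set-up, imbalances of 0.2 to 0.3 give a bias of about 4% to 9% of the service effect. These sizes rest on an assumed cut-off, SD, service effect and ePRO size, and on independent patients without country clustering. They show the mechanism and its plausible scale and do not predict the study's error. The change is worth making because it costs little.

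**What to change.** Replace the screening sentence with one adjustment set fixed in advance on subject-matter grounds, namely the full a priori list, used in every service-effect model for all outcomes and time points. Report univariate associations for description only.

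- Keep the six factors recorded at ePRO completion (occupation, education, bed sharing, sleep duration, smoking, alcohol) as proxies for status at PAP start, unless one is judged to be affected by treatment.
- Report the service comparison twice: in the ePRO population with the full set, and in the included population with the factors available from the ERP.
- Add year of PAP start, derivable from the ERP, if Multimedia Appendix 2 does not already list it.

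The cost is a change of wording, one additional model per outcome and some more coefficients. If each of the 14 comorbidities and 16 symptoms in Table 1 is entered separately, the list comes to 11 + 14 + 16 = 41 items before counting categories, or about 2,400 patients per item at 100,000 and about 730 at an assumed 30,000.
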